### Mediators

The following variables will be tested as potential mediators of intervention response: 1) cognitive flexibility, using a Stroop task [89], including Delis-Kaplan Executive Function System (D-KEFS) card nr. 4, as well as Detail and Flexibility Questionnaire (D-Flex) [90], Trail Making Test (TMT) [91], 2) response inhibition: Stop Signal Reaction Task (SSRT) [92], 3) Central coherence: Group embedded figures test (GEFT) [93], 4) Intolerance of uncertainty: Intolerance of Uncertainty Scale (IUS) [94], 5) Perfectionism: Clinical Perfectionism Questionnaire (CPQ) [95], 6) Self-efficacy: Perceived Efficacy in Patient-Physician Interactions (PEPPI-5) [96], 7) Behavioural Inhibition and Behavioural Activation Scales (BISBAS) [97], and 8) therapeutic engagement Session Rating Scale (SRS) [98].

The Stroop-task was originally developed by Stroop [89] to easily measure selective attention and cognitive flexibility. The Stroop Color-Word Test has three components. Patients are first asked to name a series of colored words to reflect basic reading rate. They are next asked to name the color (red, blue, or green) of a bar. The final component comprises a Color-Word task in which the participant is shown the names of colors printed in conflicting ink colors (e.g., the word “green” in blue ink) and is asked to name the color of the ink rather than the word. For all tasks, patients are timed by the tester to determine the number of seconds needed to identify all the stimuli, and, for the interference condition, the number of uncorrected errors is recorded. The ‘Stroop Effect’ is calculated by subtracting the difference between the interference and color patch task times, where lower scores indicate better executive functioning. Average test-retest reliability for the Stroop task is high (*r* = 0.84) [99]. In the present study we use the Color-Word interference test from the D-KEFS test-battery [100].

The D-Flex [90] is a 24-item self-report scale that measures cognitive rigidity (difficulty with set-shifting/flexibility) and attention to detail (weak central coherence). The two subscales showed high internal consistency (Cronbach α 0.90–0.95), construct validity (as compared to relevant subscales of the AQ) was strong for cognitive rigidity (*r* = 0.72) but moderate for attention to detail (*r* = 0.26).

The Trail Making Test (TMT) [91] is used to evaluate set-shifting abilities. Originally a pen-and-paper test, more recently a computerized version has become available. Patients numerically or alphabetically connect circles on a page in a ‘ dot-to-dot ’ fashion (trail A), and then alternatively link numbers and letters, i.e. 1–A–2–B–3–C (trail B). Time taken to complete trail B (switching task) is the outcome measure of set-shifting ability.

When performing the computerized Stop Signal Task (SSRT) [92] patients need to rapidly select corresponding motor responses to left- or right-facing arrows appearing on a computer screen and attempt to inhibit responses when an auditory “stop signal” sounds. Using a tracking algorithm, the task estimates the time taken to internally suppress prepotent motor responses (stop-signal reaction times).

The Group Embedded Figures Test (GEFT) [101] is a paper-and-pencil task commonly used as a measure of central coherence. The time taken to find 18 simple shapes embedded in complex designs is recorded, with the main outcome being the total time needed to locate all hidden shapes, where shorter times are assumed to result from a strong local processing capacity or a bias toward detail.

The Intolerance of Uncertainty Scale (IUS) [94, 102, 103] was developed to assess reactions to ambiguous situations, uncertainty, and future events. The IUS has been investigated and validated in various populations to measure intolerance of uncertainty. The IUS includes 27 items relating to the idea that uncertainty is unacceptable, reflects badly on a person, and leads to frustration, stress, and the inability to take action. Respondents rate items on a 5-point Likert scale ranging from 1 = “not at all characteristic of me” to 5 = “entirely characteristic of me”. The Dutch version has high internal consistency for anxiety-disordered patients (Cronbach α = 0.94) and a satisfactory test-retest reliability (*r* = 0.79).

The Clinical Perfectionism Questionnaire (CPQ) assesses degrees of perfectionism. Respondents are presented with 12 items describing different expressions of perfectionism and asked to rate these on a 4-point Likert scale in relation to the last 28 days. Total score is the sum of all scores and range from 12 to 48, with higher scores indicating higher clinical perfectionism. There is evidence showing the CPQ to be a promising and reliable measure of clinical perfectionism. It has an acceptable internal consistency (Cronbach α = 0, 71) and test-retest reliability (*r* = 0.49–0.67) [95, 104].

With the Perceived Efficacy in Patient-Physician Interactions (PEPPI-5) [96] patients rate their sense of confidence or self-efficacy in regard to their interactions with their physician on a 5-point Likert scale ranging from ‘not at all confident’ (1) to ‘very confident’ (5). The instrument has been translated and validated for use in the Netherlands [105]. The range of possible scores is 5 to 25, with 25 reflecting highest-level self-efficacy. The PEPPI-5 has a high internal consistency (Cronbach alpha 0.92) and a fair test-retest reliability (intra-class correlation coefficient 0.68).

The Behavioural Inhibition and Behavioural Activation Scale (BISBAS) [97] is a 20-item instrument designed to measure behavioural inhibition (i.e., concern over and reactivity to aversive events) and behavioural activation (i.e., responsiveness to incentives, drive, and fun seeking). Patients respond to the items using a 4-point scale, ranging from 1 (quite untrue) to 4 (quite true). After reverse scoring of two items on the BIS, subscale scores are computed by summing the scores corresponding to items on the BIS scale (7 items, range 7–28, α .74). The BAS-scale (13 items, range scores 13–52) consists of the reward responsiveness scale (5 items, α .73), the drive scale (4 items, α .76), and the Fun Seeking scale (4 items, α .66). Test-retest correlations over an 8 week period are satisfactory (r from 0.59 to 0.69). The BIS correlates moderately highly with measures of trait anxiety, negative affect, and negative temperament. The BAS correlates positively with extraversion, positive affect, and positive temperament.

The Session Rating Scale (SRS) [98] is a short, 4-item, self-report questionnaire probing therapeutic alliance. After each session patients are asked to give their impressions of the preceding session using a VAS. They rate their bond with the therapist, agreement on therapy goals and therapy tasks, and their confidence in the collaboration, where ratings can range from “there was something missing in the session today” to “Overall, today’s session was right for me”. The Dutch translation of the SRS has been shown to have a strong internal consistency (Cronbach alpha 0.85–0.95) and adequate test-retest reliability [106], although in the Dutch study correlations with outcome and concurrent validity were lower than expected.

### Moderators

The following variables will be tested as potential moderators of intervention response: 1) demographic variables (e.g. sex, age, educational level), 2) general psychopathology: Structured Clinical Interview for DSM-IV-TR Axis I disorders (SCID-I) [64], Structured Clinical Interview for DSM-IV-TR Axis II disorders, section obsessive-compulsive personality disorders (SCID-II-OCPD) [68], 3) Autism: Autism-spectrum Quotient (AQ) [107], 4) Attention-deficit hyperactivity disorder: Connors’ adult ADHD Rating Scales CAARS-S:SV) [108], 5) Cognitive flexibility: Intra dimensional-/extra dimensional shift paradigm (ID/EDS) [109], and 6) Planning ability: Behavioural Assessment of the Dysexecutive Syndrome, Zoo MAP (BADS-Zoo map) [110]. The SSRT, IUS, and BADS-Zoo map will be taken for OCD only.

The autism-spectrum quotient (AQ) [107] is a self-report questionnaire that assesses traits associated with the autistic spectrum [111]. It consists of five 10-item subscales (social skills, attention switching, communication, imagination, attention to detail). Example items of the AQ are: “I find myself drawn more strongly to people than to things” and “Trying to imagine something, I find it easy to create a picture in my mind”. Respondent rate each item on a 4-point Likert scale from “definitely agree” to “definitely disagree”. A score of ≥ 32 is indicative of an autism spectrum disorder. The index’s test-retest reliability is good (*r* = .60 to .81) and internal consistency is acceptable (α = .71) [112].

The Connors’ Adult ADHD Rating Scales self-report, short version (CAARS-S:SV) [108] comprises 30 items on the presence of ADHD symptoms to be rated on a 4-point Likert scale ranging from 0 (not at all), to 3 (very much). The maximum score for al 30 items is 90. The CAARS-S:SV consists of 5 subscales (inattention/memory problems, hyperactivity/restlessness, impulsivity/emotional lability, problems with self-concept, and ADHD-index). The internal consistency is good, ranging from α = .80 to .89 and it has an acceptable test-retest reliability (*r* = 0.58 to 0.77).

The Intra-dimensional/extra-dimensional shift task (ID/EDS) [109] is part of the Cambridge Neuropsychological Test Automated Battery (CANTAB). The version used in the current trial is a replication of the original task. The ID/EDS is a reliable and valid computerized task, which, like the TMT, probes set-shifting ability [113–115]. The paradigm involves nine-stages of a visual discrimination task with multidimensional stimuli. Two stimuli are displayed, and feedback is provided which stimulus is correct. To pass to the next stage, six consecutive correct responses are required within 50 trials; if not, the task ends. The rule for correct responding is modified at the start of each task stage.

The Zoo Map is part of the Behavioural Assessment of the Dysexecutive Syndrome test battery (BADS) [110] and consists of two parts. In the first part, patients are instructed to plan their route through a map of a zoo, visiting a selection of locations while actively disregarding others. While planning the route, patients also instructed to obey certain rules. The second part consists of the same map with the same locations that have to be visited, but this time, instructions are provided about the precise order in which the locations must be visited. Therefore, in contrast to the first part, the second part consists of a highly structured setting that strongly reduces the involvement of planning abilities. The BADS-Zoo map subtest has been proven to be a valid indicator of planning ability in a heterogeneous patient sample [116].

### Power and sample-size calculation

In accordance with Cohen [117], we calculated the sample sizes needed to detect treatment-specific differences: CRT + TAU vs. SAT + TAU, for which we used software by G-power [118].

We based effect-size calculations on Dingemans’ first RCT [57] comparing CRT + TAU with TAU alone for eating disorders in which they obtained large effect sizes for reduction in eating disorder pathology (Cohen’s d: 0.99). Given the control condition in this study we take into account a smaller effect-size. In the case of two-tailed MANOVAs, repeated measures and four within-between interactions (2 groups: AN and OCD), two conditions (CRT + TAU vs. SAT + TAU), three measurements (baseline, and 2, and 6 months after baseline), with alpha = 0.05, a sample size of 113 patients is needed to have a power of at least 0.80 to detect an effect size f(V) of 0.25. Although the dropout rate in the previous CRT studies of Dingemans was low (*n* = 7 out of 82 patients), we have opted to include an additional 15 patients to compensate for attrition, totalling 128 patients in total (64 CRT + TAU and 64 SAT + TAU).

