### Symptom-based treatment for OCD and AN

Treatment schemes for AN and OCD are generally aimed at symptom reduction. Standard treatment of adult AN consists of a combination of renourishment and psychotherapy. Clinical effects of either supportive clinical management, CBT, focal psychodynamic therapy, family therapy, or interpersonal psychotherapy are comparable [30–32]. Only 46% of patients recover fully, one third achieves partial improvement (showing residual symptoms), and 20% remains chronically ill [33]. One significant challenge in the treatment of individuals with AN concerns the ambivalence towards treatment. Intrinsic motivation to enable behavioural changes is often low [34].

According to European guidelines, the treatment of OCD should typically encompass CBT usually in combination with pharmacotherapy, specifically selective serotonin reuptake inhibitors (SSRIs) [35, 36]. Despite reasonable effect sizes (Cohen’s d around 1.0) [37–39], only 22% of OCD patients having received CBT recovers completely [37]. In a recent meta-analysis, Sharma et al. [40] found that 47% of all patients with OCD (treated or untreated) do not achieve complete remission. Thus, rates of incomplete recovery and treatment resistance remain relatively high [41, 42].

Moreover, in OCD non-compliance as to pharmacotherapy is common, as is dropout from CBT (with attrition rates between 13 and 27%) [43–47]. Dropout rates from treatment in outpatients with AN are even higher (ranging from 48 to 100%) [48].

Clearly, optimizing therapy results for AN and OCD remains a major challenge for both researchers and therapists. In the past decades various attempts have been made to develop supportive interventions to enhance adherence and effectivety, with an increasing interest in approaches that target underlying inefficiencies instead of the main symptoms of the disorder itself.

The relatively low success rates of guideline-directed therapies for AN and OCD, together with the inefficiencies in executive functioning that sufferers seem to share, have prompted the notion that patients might benefit from a training module that addresses and remediates these underlying inefficiencies.

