### Outcome measures

The primary outcome measures are: 1) disease-specific psychopathology: Eating Disorder Examination Questionnaire (EDE-Q) [70] for AN severity; Yale-Brown Obsessive Compulsive Scale (Y-BOCS) [65, 66] for OCD severity.

The Eating Disorder Examination Questionnaire (EDE-Q) [70, 71] is the self-report version of the Eating Disorder Examination (EDE) [72], a semi-structured interview to evaluate ED psychopathology. The EDE-Q assesses attitudinal and behavioural aspects of EDs over a 28-day period. It has four subscales assessing concerns about shape, weight and eating, and restraint. The EDE-Q consists of subscale scores and a total scale score. The EDE-Q has excellent internal consistency (Cronbach α 0.78-0.93). The subscales have also excellent test-retest reliability over a 2-week period (Pearson r ranging from 0.81 to 0.94) [73].

The 10-item Yale-Brown Obsessive-Compulsive Severity Scale (Y-BOCS) [74] is a clinician-rated, semi-structured interview-based scale that is broadly used to assess obsessive-compulsive symptom severity. The scale has two parts, each with five questions, with each subscale assessing five aspects of OCD pathology: 1) time consumed, 2) degree of interference, 3) distress, 4) resistance, and 5) perceived control. The first subscale gives an obsession score (maximum: 20), the second a compulsion score (maximum: 20), and together yield a total score (maximum: 40). It has a strong internal consistency (Cronbach α .88-.91), inter-rater reliability (r 0.82–0.98), and test-retest reliability in clinical and nonclinical samples were excellent.

The secondary outcome measures are: 1) disease-specific psychopathology: Obsessive-Compulsive Inventory-Revised (OCI-R) [75], 2) quality of life and daily functioning: EuroQol (EQ-5D) [76], Eating Disorder Quality of life questionnaire (ED-QoL) [77], Obsessive Compulsive Disorder Quality of life questionnaire (OCD-QoL) [78], and Work and Social Adjustment Scale (WSAS) [79], 3) cost-effectiveness (direct and indirect health-related costs as evaluated by means of patients’ self-reported QoL ratings and medical and societal burden: Trimbos/iMTA Questionnaire for Costs associated with Psychiatric illness (TiC-P) [80], 4) general anxiety: Beck Anxiety Inventory (BAI) [81], and 5) Depression: Beck Depression Inventory, second revision (BDI-II) [82].

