### Analyses

Baseline differences between the CRT and SAT (control) groups and between the participating centres are investigated using χ^2^ tests for categorical variables and ANOVAs for continuous variables. Additional exploratory analyses are conducted separately for AN and OCD.

The data for the primary AN and OCD outcome indices are analysed using linear mixed models (LMM) with the baseline value as a covariate. The mixed models analysing the general efficacy of CRT include a random term for the intercept and fixed terms for condition, time contrasts (T0–T1, T0–T2, T0–T3, T1–T2, T1–T3), and the interactions between condition and time contrasts.

In order to investigate moderators of short- and long-term treatment response, time contrasts are created (T0–T1, T0–T2, T0–T3, T1–T2, T1–T3) by means of dummy coding. Potential continuous moderator variables are standardized. Interactions between condition and the potential moderators are entered into the equation. All analyses on therapy effect modificators are of an exploratory nature. The moderator and mediator analyses are calculated with 5000 bootstraps [126].

To assess the cost-effectiveness of CRT + TAU versus SAT + TAU for ED and OCD, all relevant costs and effects are taken into account. Disease progression is described in terms of transitions between ‘states’, where a patient’s ‘state’ can shift in either direction or remain constant. Estimations of state-transition rates are based on the data from the ongoing trial and the literature, which modelling approach serves to help us assess future scenarios. Costs and effects are calculated in accordance with recommendations in the Dutch guideline for economic evaluation of health care. As a primary assessment we apply a costs-utility analysis that yields a cost per quality-adjusted life years (QALY) outcome, a common cost-effectiveness measure that allows comparison with economic evaluations of other diseases and interventions. The uncertainty estimations are computed using bootstrapping and the results expressed in an acceptability curve. If no intervention is effective, a cost-minimization calculation is performed.

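### The stated power of 0.80 belongs to a four-group omnibus MANOVA, not to the CRT-versus-SAT comparison or the planned mixed model

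*Protocol article*

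**What the plan says.** The section on power and sample size names its target: "we calculated the sample sizes needed to detect treatment-specific differences: CRT + TAU vs. SAT + TAU". The calculation it then reports is "In the case of two-tailed MANOVAs, repeated measures and four within-between interactions (2 groups: AN and OCD), two conditions (CRT + TAU vs. SAT + TAU"), with "three measurements (baseline, and 2, and 6 months after baseline"), "with alpha = 0.05", and the result that "a sample size of 113 patients is needed to have a power of at least 0.80 to detect an effect size f(V) of 0.25". Fifteen patients are added for attrition, giving 128, or 64 per arm. The Abstract splits the same 128 as 64 with AN and 64 with OCD.

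The Outcome measures section gives each disorder its own primary scale: "Eating Disorder Examination Questionnaire (EDE-Q) [70] for AN severity; Yale-Brown Obsessive Compulsive Scale (Y-BOCS) [65, 66] for OCD severity".

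The Analyses section does not use a MANOVA: "The data for the primary AN and OCD outcome indices are analysed using linear mixed models (LMM) with the baseline value as a covariate". Its fixed terms are condition, time contrasts running to T3 (12 months), and condition by time. Diagnosis is not among them. The same section describes separate AN and OCD analyses as additional and exploratory.

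**The concern.** The power statement and the planned analysis appear to describe different tests. A four-group by three-time interaction has (4 − 1) × (3 − 1) = 6 degrees of freedom. Two concern condition by time, two concern disorder by time, and two concern condition by disorder by time. Only the first pair is the comparison the section names. The omnibus test can be significant with no CRT effect at all, for example if OCD and AN respond to TAU at different speeds. Its power therefore says little about the chance of detecting an effect of CRT.

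At stake is how a null result is read. A reader would take a non-significant CRT effect, pooled or in one disorder, as coming from a trial with 80% power for it. The documents do not show that.

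**Working it through.** **Inputs.** Alpha 0.05, f(V) = 0.25, three times, two diagnoses and two conditions (Power and sample-size calculation); 64 patients per disorder (Abstract); 128 randomised, 113 evaluable. Per disorder this is 64 randomised and 113 / 2, about 56, evaluable.

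**Method.** Repeated-measures MANOVA, within-between interaction, noncentral F with Pillai's trace V, for k groups, m times and N patients:
- s = min(k − 1, m − 1)
- df1 = (k − 1)(m − 1)
- df2 = s(N − k − (m − 1) + s)
- λ = s · N · f(V)²
- f(V)² = V / (s − V)

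**Step 1: the plan's own figure.** k = 4, m = 3, so s = 2 and df1 = 6. At N = 113, df2 = 2 × (113 − 4 − 2 + 2) = 218 and λ = 2 × 113 × 0.0625 = 14.125. Power is 0.803; at N = 112 it is 0.799. So 113 is exact for this test. With the same f(V), the other layouts tried do not give it: k = 2, m = 3 needs 158; k = 2, m = 4 needs 179; k = 4, m = 4 needs 87.

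**Step 2: CRT against SAT, f(V) = 0.25 carried over.** k = 2, m = 3, so s = 1, df1 = 2, df2 = N − 3 and λ = 0.0625 N.

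| Patients | λ | Power |
|---|---|---|
| 113 (pooled, evaluable) | 7.06 | 0.65 |
| 128 (pooled, all) | 8.00 | 0.71 |
| 56 (one disorder, evaluable) | 3.50 | 0.35 |
| 64 (one disorder, all) | 4.00 | 0.40 |

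A power of 0.80 needs 158 patients in whichever population is tested.

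**Step 3: CRT against SAT, Pillai trace held fixed.** The same f(V) does not mean the same effect in both layouts. With s = 2, f(V) = 0.25 corresponds to V = 2 × 0.0625 / 1.0625 = 0.118. With s = 1 it corresponds to V = 0.0625 / 1.0625 = 0.059. Step 2 therefore halves the trace as well as changing the test. If the full 0.118 is assigned to condition, f² = 0.1176 / (1 − 0.1176) = 0.133 and λ = 0.133 N.

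| Patients | λ | Power |
|---|---|---|
| 113 (pooled) | 15.07 | 0.94 |
| 128 (pooled) | 17.07 | 0.96 |
| 56 (one disorder) | 7.47 | 0.66 |
| 64 (one disorder) | 8.53 | 0.72 |

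This is the favourable bound. It requires that AN and OCD do not differ in course or in response to CRT, which the protocol does not state.

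**Step 4: the planned model.** It adjusts for baseline, so none of these MANOVA figures is its power. The article gives no SD, target difference or baseline correlation. As an illustration only, assume 0.5 SD at one time point, with a two-sample comparison whose variance is reduced by the factor 1 − ρ². For ρ from 0.3 to 0.7, power is 0.54 to 0.79 with 32 per arm (one disorder) and 0.84 to 0.98 with 64 per arm (pooled).

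**The case against.** The arithmetic behind 113 is correct, and the trial is sized and described as one transdiagnostic study. Three points on the plan's side stand.

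- **The single-disorder reading is not settled.** A reader might infer that the trial has only about half its stated power. That is right for one disorder at f(V) = 0.25 carried over, but the Analyses section calls the separate AN and OCD analyses exploratory, which points to a pooled primary test. Against that, EDE-Q and Y-BOCS share no common scale, and the article does not say how they would enter one model. The text supports neither reading outright.
- **The shortfall depends on what is held constant.** With the Pillai trace held fixed, the pooled test exceeds 0.80. A reader might infer that the trial is underpowered for CRT against SAT; the documents do not establish this for a pooled test, where the range is 0.65 to 0.96.
- **Baseline adjustment raises power,** by an amount the article does not let us fix.

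A further inference should be resisted. The Background reports "Dropout rates from treatment in outpatients with AN are even higher (ranging from 48 to 100"%), and it is tempting to set this against the 15-patient allowance. Those are dropouts from treatment, not missing outcome assessments. The allowance rests on 7 losses among 82 patients in earlier CRT work, and 15 / 128 = 11.7% exceeds that 8.5%.

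None of this restores the 0.80 to the comparison it is attached to.

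**Conclusion.** The point holds as a mismatch between the power statement and the analysis. The 0.80 is the power of a 6-df four-group by time test, which is neither the CRT-against-SAT contrast named in the same section nor the condition by time mixed model. How far the true figure lies from 0.80 cannot be fixed from the article. At f(V) = 0.25 carried over, it is 0.65 to 0.71 pooled and 0.35 to 0.40 per disorder; with the whole Pillai trace of 0.118 due to condition, it is 0.94 to 0.96 pooled and 0.66 to 0.72 per disorder. These ranges assume three times, equal arms, no baseline adjustment, and 113 to 128 patients pooled or 56 to 64 per disorder. Under both effect-size assumptions the single-disorder MANOVA stays below 0.80; the pooled test may lie on either side.

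**What to change.** 1. Stop presenting 0.80 as the power for CRT + TAU against SAT + TAU; label it as the power of the four-group by time interaction.
2. State whether the primary contrast pools the two disorders or is made within each. If pooled, say how EDE-Q and Y-BOCS are brought into one model and how diagnosis is handled.
3. Print the power of that contrast under the planned baseline-adjusted mixed model, with the assumed effect size and baseline correlation, and give the per-disorder power beside it.

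This is a rewording of the power section and a clarification of the Analyses section. It needs no extra patients and does not in itself require a new standardised primary outcome, which would be a debatable change in an ongoing trial. The cost is that the stated figure will probably be less favourable, at least for each disorder alone.
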